## Other Anti-tumor/Cancer or Investigational Drugs

Subjects are prohibited from receiving the following treatments during the treatment period of this study:

- Systemic chemotherapy and biologic therapy (including antitumor agents with immunomodulatory effects, including but not limited to, e.g., interferon, interleukin-2, thymosin, immune cell therapy, etc.).
- Immunotherapy not specified in this protocol.
- Drugs other than those specified in this study, including proprietary Chinese medicines with clear antitumor indications.
- Radiation therapy (Note: Sponsor may approve and allow radiation therapy to symptomatic isolated lesions or to the brain as long as it is not a lung or target lesion.).
- Live vaccines, including, but not limited to, the following: measles, mumps, rubella, varicella, yellow fever, rabies, BCG, and typhoid (oral) vaccines, within 28 days prior to the first dose of study medication of the study treatment and during participation in the study. Inactivated viral vaccines for seasonal influenza, administered by injection, are permitted; however, live attenuated influenza vaccines administered intranasally are not permitted.
- Corticosteroids, Inhaled steroids allowed for use in the treatment of asthma or chronic obstructive pulmonary disease (COPD) as part of stationary therapy. Corticosteroids for the management of potential irAE are allowed. Physiologic doses of corticosteroids are allowed. Allow prophylactic corticosteroids to avoid allergic reactions (e.g., intravenous contrast media).

Subjects requiring any of the above treatments, as assessed by the investigator, should be excluded from the study. Subjects may receive other medications as deemed medically necessary by the investigator. It is important for the investigator to review each medication (prescription and non-prescription) received by the subject prior to study entry and at each study visit.

At each visit, subjects must be asked about any new medications they have received since the previous visit;

In order to reduce the risk of drug interactions, all measures must be taken to limit the number of concurrent administrations that are truly necessary;

Drugs that are hepatotoxic (i.e., drugs with warnings of hepatotoxicity in the product insert) should be avoided during administration. Investigators are encouraged to review the potential hepatotoxicity of each drug by searching the [www.livertox.nih.gov](http://www.livertox.nih.gov/) website.

# STUDY PROCEDURES

Each patient has to go through three phases to complete this clinical study after signing the informed consent form: screening period, treatment period, and follow-up period. Before starting the study, patients must read and sign the Ethics Committee (EC)-approved informed consent form. All study steps were required to be performed within the time window specified in the trial flow chart. All observations and examination times are independent of the length of discontinuation of the drug, and the relevant examinations will be performed at each session as specified.

## Screening Period

**The investigator will enroll subjects as follows.**

Obtain an ICF with the subject's signature prior to any study-related processes. Subjects were formally determined to be eligible for enrollment after review of the inclusion/exclusion criteria by the principal investigator or a designated person authorized by the principal investigator with appropriate training.

Subjects who do not meet the relevant criteria for this study (screening failure) may receive rescreen. Each subject may be rescreened once again. At the time of rescreening, the subject must re-sign the ICF and will be reassigned a subject identification number.

If a subject is discharged from the group or is ineligible for enrollment due to early onset of PD, withdrawal of ICF, or intolerance without 28 days of observation, the principal investigator of the group leader unit will decide whether or not to replenish the subject, as appropriate.

**Procedures for incorrectly enrolled subjects**

Enrollment criteria must be strictly adhered to. If a subject is found to be enrolled who does not meet the enrollment criteria, the Principal Investigator is required to discuss and determine whether or not to continue the subject's participation in this study with or without the study drug. If the investigator determines that it is medically appropriate for the subject to remain in the study and the drug provider agrees with the investigator's decision, the subject may continue to participate in the study and receive the study drug. If the Investigator determines that it is medically appropriate for the subject to remain in the study, but the drug supplier disagrees with the Investigator's determination, the subject may not continue to participate in the study (with or without treatment with the study drug). Refer to Table 7 for the screening visit process.

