**Table 8. Treatment Visits Process**

| **Treatment Period** | **Cycle 1**  **D1** | **Cycle 2**  **D1±3** | **N^th^ cycle**  **D1±3** | **Note** |
| --- | --- | --- | --- | --- |
| Laboratory Tests and AE Assessment | X | X | X | All AEs that occur after signing the informed consent form to 30 days after the last dose must be monitored and documented. If a subject starts a new anti-tumor treatment during the AE collection period, then only treatment-related AEs should be collected after the start of new anti-tumor treatment. |
| Concomitant Medications | X | X | X | All concomitant medications/treatments from 28 days prior to study treatment until the end of the safety follow-up period should be collected. If a subject starts a new systemic anti-tumor treatment during the study, then only concomitant medications/treatments used for study treatment-related AEs should be documented. |
| Evaluation of Efficacy | | | | |
| Imaging Evaluation |  | X | X | Refer to section12.3 and 12.4 |
| Infusion of Study Drugs | | | | |
| Camrelizumab | 200mg IV, Q3W | | | Refer to section 8. |
| Apatinib | 250mg PO QD | | | Refer to section 8. |
| Carboplatin | AUC 5 mg/mL/min IV Q3W | | | Refer to section 8. |
| Etopside | 100 mg/m2 IV Day 1-3 Q3W | | | Refer to section 8. |

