## Adverse Event

Adverse Event (AE) Definition: an AE is any unfavorable medical event that occurs after a subject or clinical trial participant receives a drug or treatment regimen that is not necessarily causally related to the treatment.

AE can be any sign (including abnormal laboratory test results), symptom, or disease that is unpleasant or unrelated to the purpose for which the product was used, whether or not it is considered to be related to the medical product, that is temporally related to the use of the medical product.

Events that occur during the pre- and post-treatment phases are also considered AEs under the regulations. Therefore, safety monitoring of AE or reporting of SAEs should begin once the subject participants in(signs the informed consent form) and continue through the end-of-trial visit.

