## SAE's Reporting Procedures

Serious adverse events should be reported from the time the subject signs the informed consent form up to and including the 30th calendar day after the last dose of study drug. During the trial period, if a serious adverse event occurs, it must be reported to the clinical supervisor and the principal investigator within 24 hours, and at the same time fill in the "Serious Adverse Event (SAE) Report Form ", sign and date it.

All serious adverse events must be reported. Serious adverse events occurring more than 30 days after the last dose are generally not reported unless they are suspected to be related to the study drug.

Serious adverse events should be recorded in detail with symptoms, severity, time of occurrence, time of treatment, measures taken, and follow-up time and modality and regression. If the investigator believes that a serious adverse event is not related to the test drug but is potentially related to a study condition (e.g., termination of the original treatment, or comorbidities during the course of the trial), this relationship should be detailed in the narrative portion of the Serious Adverse Event page of the Medical Record Report Form. If the intensity of a particular ongoing serious adverse event or its relationship to the subject drug changes, a follow-up report of the serious adverse event should be sent immediately. All serious adverse events should be followed until recovery or stabilization.

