## Statistical Analysis of Data Sets

Full Analysis Set (FAS): the efficacy of all cases enrolled and using the drug at least once was analyzed according to the principle of Intentional Analysis (ITT).

Efficacy Analysis Set (EAS): Patients who patients who received at least one dose of study drug and had at least one post-treatment tumor evaluation constituted the evaluable analysis set (EAS) population.. The efficacy of the drugs was statistically analyzed by both FAS and PPS.

Safety Analysis Set (SAS): all enrolled cases, all patients who have used the trial drug at least once and have a post-dose safety record. This data set is used for safety analysis.

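### Section 11.1 lets the drug supplier end an incorrectly enrolled subject's participation altogether, even off drug, with no carve-out for dosed subjects, which contradicts the follow-up and analysis-set rules elsewhere in the protocol

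*Protocol*

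**What the plan says.** The procedure in section 11.1 is triggered as follows: "If a subject is found to be enrolled who does not meet the enrollment criteria". It applies to any enrolled subject, dosed or not. The principal investigator must first decide "whether or not to continue the subject's participation in this study with or without the study drug", so at that point participation and study drug are two separate questions.

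Two outcomes follow when the investigator considers it medically appropriate for the subject to remain. If the supplier agrees, the subject stays and receives study drug. If the investigator favours remaining "but the drug supplier disagrees with the Investigator's determination", then "the subject may not continue to participate in the study (with or without treatment with the study drug". The procedure sets no time limit on this step and does not mention follow-up.

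Elsewhere the protocol sets duties after treatment without an exception for these subjects:

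- Table 8, with equivalent wording in Tables 7, 9 and 10: "All AEs that occur after signing the informed consent form to 30 days after the last dose must be monitored and documented".
- Section 13.2: safety monitoring starts at consent and is to "continue through the end-of-trial visit".
- Section 13.7: serious adverse events are reported "up to and including the 30th calendar day after the last dose of study drug", and later if suspected to be drug-related.
- Section 14.3: the full analysis set is "all cases enrolled and using the drug at least once".

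**The concern.** Stopping a drug and stopping observation are different decisions. The first rule in section 11.1 keeps them apart; the last rule merges them, and gives the deciding voice to the party that supplies the drug, over the investigator's medical judgement. For a subject not yet dosed, little is lost. For a subject already dosed, a site that follows section 11.1 literally would end the observation that the rest of the protocol requires.

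Safety is the primary endpoint (section 2.1), and PFS and OS are secondary endpoints, in a single-arm trial of 36 subjects. A dosed subject who is removed still counts in the full analysis set, but the data needed to analyse that subject may no longer be collected. A statistical analysis plan cannot recover data that the protocol told sites not to collect.

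**Working it through.** The protocol gives no figure to reproduce, so the check sets the passages side by side.

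**Step 1: scope of the bar.** One might read the supplier's role as control of drug supply only. The closing parenthesis in section 11.1 excludes that reading, because it bars participation without study drug as well. Off-drug participation in this trial can only mean observation.

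**Step 2: duties that the bar meets.**

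| Duty | Where | What ends it, as written | Exception for supplier disagreement? |
|---|---|---|---|
| End-of-treatment visit, within 3 days either side of the decision | 11.3 | Triggered by stopping treatment or leaving the study | None |
| AE capture | Tables 7 to 10 | 30 days after the last dose; only treatment-related AEs once new antitumour therapy starts | None |
| SAE reporting | 13.7 | Day 30 after the last dose; later if suspected related; followed to recovery or stabilisation | None |
| Safety visit | 11.4, Table 10 | One visit after the last dose | None |
| Imaging after stopping for reasons other than imaging progression, as far as possible | Table 10 | New antitumour therapy, progression, withdrawal of consent, death | None |
| Survival status every 3 months | Table 10, Schedule of Activities | No stopping rule stated | None |
| Membership of the full analysis set | 14.3 | At least one dose is enough | None |

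A site cannot both end all participation and carry out the observation in this table.

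**Step 3: which data are most exposed.** The short-term safety data have some protection: section 11.3 attaches a visit to leaving the study itself, and AE and SAE capture runs to day 30 regardless. The later items have less.

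- *Safety visit.* Section 11.4 places it at 90±7 days after the last dose, so at the earliest 90 − 7 = 83 days. Table 10 gives 42±7 days, so at the earliest 42 − 7 = 35 days. Both fall after day 30, so the AE window does not protect the visit. The Schedule of Activities gives 30 days. The three timings disagree and also need to be reconciled.
- *Imaging and survival.* Both extend well beyond day 30, and no clause says that they continue for a subject barred from the study.

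**Step 4: scale.** The planned sample size is 36 (section 4). The number of dosed subjects removed this way is not given, so 1 to 3 is an assumption:

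- 1/36 = 2.8%
- 2/36 = 5.6%
- 3/36 = 8.3%

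These are shares of the cohort whose later follow-up could be lost. They are not estimates of bias.

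**The case against.** The strongest reply is that the protocol uses leaving the study loosely. Section 11.3 equates end of treatment with withdrawal from the study. Section 6 lists imaging progression and intolerable toxicity as withdrawal criteria, yet section 3.1 sends subjects who stop for those reasons on to survival follow-up. On that reading, a subject barred under section 11.1 would still be covered by sections 11.3, 11.4 and 13.7, and supplier disagreement is not among the events that end imaging in Table 10. Much of this stands: it shows that the protocol does not consistently intend leaving to mean the end of observation. It does not remove the conflict, because section 11.1 goes further than section 6 and expressly bars off-drug participation.

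A reader might infer several stronger things that the documents do not support:

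- *That follow-up stops by rule.* No passage says so. It is the plain effect of the bar, and other passages point the other way.
- *That a removed patient has no toxicity follow-up.* The 30-day AE and SAE rules and the end-of-treatment visit contain no exception.
- *That the procedure concerns treated or higher-risk subjects.* It covers any ineligible enrolled subject. Breaches of the bleeding, cardiac or organ-function criteria may carry more risk; breaches of the age limit or the measurable-lesion criterion need not.
- *That removal would be driven by outcome.* The absence of a time limit makes this possible, but the step needs a real eligibility breach and goes first to the principal investigator.
- *That the primary result shifts by a known amount.* Suppose the true count of subjects with grade ≥3 events is 18/36 = 50% (exact 95% CI 32.9% to 67.1%) and two such events go unrecorded. The report would be 16/36 = 44.4%, or 16/34 = 47.1% if both subjects left the denominator. All these counts are assumed, both results lie well inside the interval, and the denominator of 34 conflicts with section 14.3 if the subjects have a post-dose safety record.
- *That PFS and OS would be informatively censored.* This depends on censoring rules that may sit in an analysis plan not shown here.

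**Conclusion.** The point holds as a contradiction within the protocol. Section 11.1 lets the supplier end participation entirely, on or off drug and against the investigator's judgement, with no carve-out for dosed subjects. Sections 11.3, 11.4, 13.2 and 13.7 and Tables 7 to 10 require observation of those subjects to continue, and section 14.3 keeps them in the full analysis set, and in the safety set if they have a post-dose safety record.

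The best-supported potential losses are later imaging, the later safety visit and survival follow-up. The size is unknown: each subject is 2.8% of the planned cohort, and the event may be rare or never occur. The conclusion rests on reading the bar in section 11.1 by its plain words. If the sponsor meant only that supply of drug ends, the text does not say so and should. The change is worth making because safety is the primary endpoint, the cohort is small and the correction is cheap.

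**What to change.** Leave the decision on study drug as section 11.1 provides, and reword the supplier-disagreement sentence so that it does not end observation. Then add that any subject who has received at least one dose:

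- stays under the AE and SAE collection, tumour assessment and survival follow-up already scheduled in sections 11.3, 11.4 and 13.7, unless consent is withdrawn;
- remains in the analysis sets as section 14.3 defines them;
- is reported as a protocol deviation.

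Deleting the parenthesis alone would not be enough, because the sentence would still bar the subject from participating. The statement on analysis sets only confirms what section 14.3 already implies; the sentence on continued follow-up is the one that changes practice.

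The cost is about two sentences in section 11.1, submitted as a protocol modification to the ethics committee as section 16 requires. No visit or assessment is added, since the follow-up is already scheduled for other subjects who stop treatment.

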**Table 7. Screening Visits Process**

| **Screening period** | **-28-1 days** | **-7-1 days** | **Note** |
| --- | --- | --- | --- |
| Baseline | | | |
| Written Informed Consent Form | X |  | For those who did not meet the relevant criteria for this study subjects may be rescreened. |
| Inclusion/Exclusion Criteria | X |  | Refer to section 5.1 and 5.2 |
| Demographics/Medical History/Previous Medications | X |  | Prior medications include treatments for the initial diagnosis, including chemotherapy, radiation therapy, and surgical treatments, the time of the latter antitumor treatment must be recorded. |
| Vital Signs | X |  | Vital signs include: temperature, pulse, respiratory rate and blood pressure. |
| Weight, Height | X |  | Refer to section 13.1.2 |
| Physical Examination | X |  | Refer to section 13.1.2 |
| ECOG PS Sore | X |  | Refer to section 13.1.2 |
| Laboratory tests | | | |
| 12-lead ECG | X |  | Refer to section 13.1.2 |
| Hematology/Blood Biochemistry Urinalysis/Urine  Routine/Stool Tests |  | X | Refer to section 13.1.1 |
| Coagulation Function |  | X | Refer to section 13.1.1 |
| Pregnancy Test |  | X | Refer to section 13.1.2 |
| Thyroid Function Test | X |  | Refer to section 13.1.2 |
| Myocardial Enzyme Test |  | X | Refer to section 13.1.2 |
| Pituitary-adrenal axis Test | X |  | For hospitals where conditions permit |
| HIV, HBV and HCV Test | X |  | Refer to section 13.1.2 |
| Echocardiography |  | X | Refer to section 13.1.2 |
| Pulmonary Function Tests and Arterial Blood Gas (ABG) Analysis | X |  | Refer to section 13.1.2 |
| AE Assessment | X |  | The safety assessments for AEs and laboratory tests will be performed according to NCI CTCAE v5.0. All AEs that occur after signing the informed consent form to 30 days after the last dose must be monitored and ocumented. If a subject starts a new anti-tumor treatment during the AE collection period, then only treatment-related AEs should be collected after the start of new anti-tumor treatment. |
| Concomitant Medications | X |  | All concomitant medications/treatments from 28 days prior to study treatment until the end of the safety follow-up period should be collected. If a subject starts a new systemic anti-tumor treatment during the study, then only concomitant medications/treatments used for study treatment-related AEs should be documented. |
| Evaluation of Efficacy | | | |
| Imaging Evaluation | X |  | Refer to section12.3 and 12.4 |

## Treatment period

Subjects who met the inclusion criteria and did not meet any of the exclusion criteria and signed the informed consent form were enrolled in the treatment period after passing the baseline examination. The investigator will administer the study drug according to the protocol and will monitor the subject for any adverse reactions and efficacy, which will be promptly recorded in the original medical record. Refer to Table 8 for the flow of visits during the treatment period.

**Table 8. Treatment Visits Process**

| **Treatment Period** | **Cycle 1**  **D1** | **Cycle 2**  **D1±3** | **N^th^ cycle**  **D1±3** | **Note** |
| --- | --- | --- | --- | --- |
| Laboratory Tests and AE Assessment | X | X | X | All AEs that occur after signing the informed consent form to 30 days after the last dose must be monitored and documented. If a subject starts a new anti-tumor treatment during the AE collection period, then only treatment-related AEs should be collected after the start of new anti-tumor treatment. |
| Concomitant Medications | X | X | X | All concomitant medications/treatments from 28 days prior to study treatment until the end of the safety follow-up period should be collected. If a subject starts a new systemic anti-tumor treatment during the study, then only concomitant medications/treatments used for study treatment-related AEs should be documented. |
| Evaluation of Efficacy | | | | |
| Imaging Evaluation |  | X | X | Refer to section12.3 and 12.4 |
| Infusion of Study Drugs | | | | |
| Camrelizumab | 200mg IV, Q3W | | | Refer to section 8. |
| Apatinib | 250mg PO QD | | | Refer to section 8. |
| Carboplatin | AUC 5 mg/mL/min IV Q3W | | | Refer to section 8. |
| Etopside | 100 mg/m2 IV Day 1-3 Q3W | | | Refer to section 8. |

## End of Treatment

End of treatment refers to withdrawal from the study. An end-of-treatment visit is required ± 3 days from the time of the decision to terminate treatment and/or withdraw from the study. Refer to Table 9 for the flow chart for end-of treatment visits.

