# STUDY DESIGN

## Schematic Design

This study is a prospective, multi-cohort clinical trial designed to evaluate the safety and efficacy of chemotherapy(Etoposide + Carboplatin) in combination with the PD-1 antibody camrelizumab and the anti-angiogenic drug apatinib in the treatment of patients with extensive stage small cell lung cancer.

Study objectives: To explore the safety of induction chemotherapy followed by chemotherapy combined with immune and anti-angiogenic drugs for the first-line treatment of patients with ES-SCLC; (2) To explore the efficacy of induction chemotherapy followed by chemotherapy combined with immune and anti-angiogenic drugs for the first-line treatment of patients with ES-SCLC; (3) To explore the precision treatment population of patients with extensive small cell lung cancer treated with chemotherapy combined with immunological and anti-angiogenic agents after induction chemotherapy.

If subjects did not withdraw consent from the trial or were deemed by the investigator to be unsuitable for further trials, and each subject will be treated until disease progression or, drug-induced toxicities are intolerable, followed by a survival follow-up period.

[figure not shown]
(1) Etoposide: 100 mg/m2 IV Day 1-3; Carboplatin: AUC 5 mg/mL/min IV Day 1; Camrelizumab: 200 mg IV Day 1; Apatinib: 250 mg Po QD.

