# WITHDRAWAL CRITERIA

- Subjects withdrew informed consent.
- Progression of the disease on imaging.
- Those who cannot tolerate toxicity.
- Subjects missed visits or had positive blood HCG;
- Other situations where the investigator felt it necessary to withdraw from the study.

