**Table 10. Safety Follow-up Process**

| **Safety Follow-Up** | **42±7 days** | **Note** |
| --- | --- | --- |
| Vital Signs | X | Vital signs include: temperature, pulse rate, respiratory rate and blood pressure.  Refer to 13.1.2 |
| Weight | X | Refer to 13.1.2 |
| Physical Examination | X | Refer to section 13.1.2 |
| ECOG PS Score | X | Refer to section 13.1.2 |
| Laboratory Tests | | |
| 12-lead ECG | X | Refer to section 13.1.2 |
| Hematology/Blood Biochemistry/Urine /Stool Test | X | Refer to section 13.1.1 |
| Coagulation Function | X | Refer to section 13.1.1 |
| Thyroid Function Test | X | Refer to section 13.1.2 |
| AE Assessment | X | All AEs that occur after signing the informed consent form to 30 days after the last dose must be monitored and documented. If a subject starts a new anti-tumor treatment during the AE collection period, then only treatment-related AEs should be collected after the start of new anti-tumor treatment. |
| Concomitant Medications | X | All concomitant medications/treatments from 28 days prior to study treatment until the end of the safety follow-up period should be collected. If a subject starts a new systemic anti-tumor treatment during the study, then only concomitant medications/treatments used for study treatment-related AEs should be documented. |
| End-of-Treatment Visits | | |
| State of Survival | X | Once every 3 months after finished treatment. |
| Follow-up Anti-Tumor Therapy | X |  |
| Evaluation of Efficacy | | |
| Imaging Evaluation | X | For discontinuation of therapy for reasons other than imaging PD, imaging evaluations will be performed according to the imaging evaluation time cutoffs, to the extent possible, until either of the following events occurs: initiation of a new antitumor therapy, PD, subject withdrawal of ICF, and death. |

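### End of treatment is defined as withdrawal from the study, which contradicts the survival and imaging follow-up that the protocol schedules after treatment and that OS, PFS and DoR need

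*Protocol*

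**What the plan says.** Two groups of statements in the protocol bear on what happens when a subject stops treatment.

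**Statements that end participation.** Section 11.3 opens with "End of treatment refers to withdrawal from the study". Section 6, repeated in the abstract, lists among the withdrawal criteria "Progression of the disease on imaging", "Those who cannot tolerate toxicity" and "Subjects missed visits or had positive blood HCG". No number or duration of missed visits is given. The list closes with "Other situations where the investigator felt it necessary to withdraw from the study", so it reads as a list about the study and not only about the drugs.

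**Statements that continue observation.** Section 3.1 has subjects treated until progression or intolerable toxicity, "followed by a survival follow-up period". The Schedule of Activities places survival follow-up every 3 months after end of treatment and safety follow-up. Section 11 says that every patient passes through screening, treatment and follow-up. Table 10 asks for survival status every 3 months after treatment. On scans it says: "For discontinuation of therapy for reasons other than imaging PD, imaging evaluations will be performed according to the imaging evaluation time cutoffs". It qualifies this as being to the extent possible, and ends the scans at new antitumor therapy, progression, withdrawal of the informed consent form, or death.

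The second sentence of section 11.3 times the visit from "the decision to terminate treatment and/or withdraw from the study", which treats the two as separate events.

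Section 12.2 defines OS to death from any cause, PFS to progression or death, and DoR from first response to progression or death. Section 14.4 estimates PFS and OS by Kaplan-Meier.

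**The concern.** A subject cannot both have left the study and still be scanned and followed in it. Read literally, sections 6 and 11.3 end observation at the point where section 3.1 and Table 10 say that it continues, and no order of precedence is given.

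The stake is the time-to-event endpoints. Kaplan-Meier assumes that censored subjects have the same later risk as those who remain. Subjects withdrawn at progression generally carry a higher risk of death than those still progression-free, so censoring them there would probably make OS look too favourable. Subjects withdrawn for toxicity or missed visits may also differ in prognosis from those who stay. Data not collected after treatment cannot reliably be recovered by analysis.

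**Working it through.** **Step 1. Compare the two groups of statements by reason for stopping.** The protocol states no figure on this point that could be reproduced, so the check is mainly textual.

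| Reason for stopping | Sections 6 and 11.3 read literally | Follow-up provisions | Endpoint lost under the literal reading |
| --- | --- | --- | --- |
| Imaging progression | Withdrawn from the study | Survival follow-up (section 3.1, Schedule, Table 10) | OS only; the PFS event, and for responders the end of DoR, is already recorded |
| Intolerable toxicity, no progression | Withdrawn from the study | Survival follow-up (section 3.1, Schedule, Table 10) and continued scans (Table 10) | PFS and OS; DoR for responders |
| Missed visits, no progression | Withdrawn from the study, no threshold | Survival follow-up and scans under the general wording of Table 10; not named in section 3.1 | PFS and OS; DoR for responders |

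In each row the two readings give different data for the same subject. Section 11.3 is also inconsistent within itself: its first sentence equates two events that its second sentence separates.

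Section 13.6 adds a further case. A subject who becomes pregnant is to be withdrawn from the study at once and then followed through pregnancy and postpartum. There the protocol states expressly that observation continues after withdrawal. Sections 6 and 11.3 carry no such clause.

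**Step 2. How many deaths full follow-up would be expected to yield.** This sets the scale of the information at stake. It does not estimate the loss.

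Inputs:
- Sample size 36 (section 4).
- Enrolment 2021.2 to 2022.2 and follow-up to 2023.03 (section 17). Counting month to month, follow-up is 13 months for the last subject and 25 for the first.
- Median OS of 10.8 months (chemotherapy plus pembrolizumab) and 9.3 months (a chemotherapy comparator arm), both from section 1. A median of 15 months is an assumed optimistic value.
- Assumed: uniform accrual, exponential survival, no other loss to follow-up.

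Formula, with λ = ln 2 / m:

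Expected deaths = 36 × (1 − S̄), where S̄ = (e^(−13λ) − e^(−25λ)) / (12λ).

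| Median m (months) | λ | S̄ | Expected deaths |
| --- | --- | --- | --- |
| 9.3 | 0.0745 | (0.379 − 0.155) / 0.894 = 0.251 | 27.0 |
| 10.8 | 0.0642 | (0.434 − 0.201) / 0.770 = 0.303 | 25.1 |
| 15 | 0.0462 | (0.548 − 0.315) / 0.555 = 0.421 | 20.8 |

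Full follow-up would therefore give about 25 deaths, with a range of 21 to 27. How many would be missed depends on how many subjects stop for each reason and which text each site follows. The documents give neither.

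**The case against.** The strongest reply is that the intent is plain. Follow-up appears in section 3.1, section 11, the Schedule and Table 10. Section 9.2 says that progression means permanently stopping treatment. Table 10 names withdrawal of the informed consent form separately from stopping therapy. Section 17 plans follow-up of all enrolled patients. A site that closed a record at progression would have to disregard all of these. The abstract names only a primary centre and one participating site, so scope for divergent practice is limited. The primary endpoint is safety, and adverse event collection to 30 days after the last dose is stated separately. OS and PFS are secondary and mainly descriptive.

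Most of this stands. Discontinuation of treatment is the likely intent, and the defect is a contradiction in wording, not missing follow-up. The reply does not remove the contradiction, because no sentence says that a subject who meets a section 6 criterion stays in follow-up. The ambiguity is greatest for missed visits, which section 3.1 does not mention.

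Three stronger readings are tempting and are not supported:
- **That PFS is also biased by withdrawal at progression.** It is not, because the event has been recorded by then. Harm to PFS can come only from the toxicity and missed-visit routes, whose frequency is not given.
- **That only about 4 to 7 deaths would be captured.** This takes an assumed 10 to 20% of 36 PFS events as deaths (0.10 × 36 = 3.6; 0.20 × 36 = 7.2). It needs every subject to have an observed PFS event and every site to withdraw at progression. The share is not in the documents. The figure also leaves out deaths after progression that section 13.6 requires to be reported within the safety period. It is a worst case, not an estimate.
- **That sites did close records at progression.** The documents do not show what any site did.

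**Conclusion.** The point holds as an internal contradiction. Section 11.3, with section 6 and the abstract, conflicts with section 3.1, section 11, the Schedule and Table 10, and section 11.3 conflicts with its own second sentence.

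Under the literal reading, OS is exposed at every stopping reason examined, and PFS and DoR are exposed when subjects stop for toxicity or missed visits. The censoring would probably be informative. That is a judgement about prognosis, not something the documents quantify. The deaths at stake number about 25 of 36 (21 to 27) on the stated exponential and accrual assumptions. The number lost could lie anywhere from none, if sites follow Table 10, to a large share, if they follow sections 6 and 11.3. The contradiction itself does not depend on these figures.

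**What to change.** Reconcile section 6, section 11.3, the abstract and the pregnancy paragraph of section 13.6 with section 3.1, section 11, the Schedule and Table 10.

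1. Replace the opening sentence of section 11.3 with a definition along these lines: *End of treatment means permanent discontinuation of study treatment. It is not in itself withdrawal from the study or withdrawal of consent.*
2. State in section 6 and the abstract that, unless consent to follow-up is withdrawn, subjects who end treatment, including those who missed visits, stay in the 3-monthly survival follow-up already scheduled.
3. State that those who stopped without imaging progression also stay in the imaging already described in Table 10, with its existing limits: to the extent possible, and until new antitumor therapy, progression, withdrawal of the informed consent form, or death.
4. Leave to the sponsor which clinical criteria stop treatment and how pregnancy is handled. Section 13.6 has its own withdrawal and follow-up provision, and nothing here proposes scans for subjects who become pregnant.

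The cost is a wording amendment. It adds no visits, scans or subjects beyond those the protocol already schedules, and it changes no analysis method.
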